**Fig 1 pone.0324590.g001:**
[figure not shown]
The schedule of enrolment, interventions, and assessments.

**Fig 2 pone.0324590.g002:**
[figure not shown]
The Consolidated Standards of Reporting Trials flow diagram.

The patients will be blinded to the group allocation as they are under general anesthesia. Surgeons will not be aware of the specifics of the fluid replacement throughout the procedure, even if they can see what the anesthesiologist is monitoring. The anesthesiologists responsible for the patient cannot be blinded as they have to provide fluids according to the study protocol. The statistician analyzing the outcomes will be unaware of the group to which the data pertains.

In the event of a critical occurrence during surgery, such as cardiac arrest or significant arrhythmias resulting in hemodynamic instability, the anesthesiologist will promptly notify the surgeon and disclose the patient allocation group.

### Preoperative preparation and informed consent process

The patients will be assessed by anesthesiology residents a day before the surgery. They will be advised about fasting, anesthesia, and surgical steps, the possibility of intubation postoperatively, and admission to neurosurgical ICU. The study protocol will be informed and requested for consent. Certain medications, such as antihypertensives, steroids, antibiotics, and anticonvulsants, will be maintained until the day of surgery. Sedative or anxiolytic medications are not administered routinely but will be evaluated on a case-by-case basis.

### Anesthesia protocol

At the operation theater, the patients will receive standard ASA monitoring including electrocardiogram (ECG), pulse oximetry (SpO_2_), non-invasive blood pressure, temperature, end-tidal CO_2_ (etCO_2_), Bi-Spectral index (BIS), direct arterial pressure, and central venous pressure (CVP). Two large-bore peripheral venous lines will be established. All patients will have general anesthesia with endotracheal intubation. The target control infusion (TCI), Schnider model, will be used for the total intravenous anesthesia (TIVA) technique. The effect-site concentration of propofol will be started at 6–8 μg.ml^−1^. Tracheal intubation will be facilitated with cis-atracurium 0.2 mg.kg^−1^ and then maintenance infusion dose at 2 μg.kg^−1^.min^−1^ throughout the procedure. Cisatracurium is only used for intubation and not for infusion in certain cases where surgeons need to monitor cranial nerves, such as tumor resection in the CPA region, since it could interfere with the assessment of motor function of those cranial nerves. A mixture of oxygen and air will be used during anesthetization. The patients will receive an intermittent bolus dose of fentanyl, 2–3 μg.kg^−1^. Post-induction, a 20-G arterial catheter will be placed into the radial artery of the arm corresponding to the side of the lesion, which will be positioned on top when the patient is arranged in the park bench position. A 7-Fr, triple-lumen central venous catheter will be inserted in the right subclavian vein, under ultrasound guidance, for the CVP monitoring. Plain bupivacaine 0.5%, 10 ml, will be injected over the nerves supplying the scalp on the surgical side, including the pre-auricular nerve and the greater and lesser occipital nerves. The anesthesiologist will provide 2 ml of 2% lidocaine at each of the three pre-marked locations, five minutes before the surgeon applies the Mayfield head holder. The neuro-surgical resident will insert a urinary catheter. The patient will be carefully positioned on the park bench. The endotracheal tube, intravenous line, arterial line, and CVP line will be re-checked after the position is finalized. The ventilator setting (Maquet Critical Care AB, Sweden) is tidal volume 8 ml.kg^-1^(ideal body weight), respiratory rate will be adjusted to keep normocarbia (etCO_2_ 35–40 mmHg), inspiration: expiration ratio 1:2, positive end-expiratory pressure (PEEP) 5 cmH_2_O, and a fraction of inspired oxygen of 0.5 with air mixture. The intraoperative parameters including heart rate, arterial blood pressure, PPV, and CVP, will be recorded on the Mindray, BeneVision N12 (Shenzhen Mindray Bio-Medical Electronics). The anesthetic depth will be monitored using a BIS monitor (Covidien Ireland Limited) and maintained between 40–60 throughout the operation. Serum blood lactate levels will be evaluated hourly using arterial blood gas analysis throughout the surgical procedure. Mannitol is not routinely given to every patient; it depends on the surgeon’s decision. During the surgery, the patient will receive fluids following the fluid management protocol, contingent upon their classification into the PPV or CVP fluid guidance group. At the end of the surgery, should the patient receive muscle relaxants, they will be antagonized with neostigmine at 0.05 mg. kg-1 and glycopyrrolate at 0.01 mg.kg^-1^. The patient must meet the safe extubation criteria; otherwise, if the surgeon determines that extubation is premature, the patient will stay intubated state and be transferred to the neuro-ICU. The surgeon will be asked to rate the brain relaxation, using a four-point scale (1 = relax, 2 = satisfy, 3 = firm, 4 = bulging) [20]. At the ICU, the anesthesiologist will examine the conjunctival edema, peri-orbital swelling, and the cuff leakage test, if the patient is in the intubated state.

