### Ethical considerations

This study protocol has been approved by the Institutional Ethical Committee of the Faculty of Medicine, Chiang Mai University (CMU), with the protocol number ANE-2567-0391. All participants must provide consent to engage in the study once the research team thoroughly elucidates the study methodology. The results of this study will be published in a peer-review journal. Participants involved in the research may directly request the study results from the researchers upon publication. No additional blood work is required beyond the standard practice for patients undergoing SOC to remove tumors. Participants will be monitored in accordance with established standards of anesthesia care and treated in compliance with the Declaration of Helsinki. Confidential information will be securely stored throughout the duration of the study and thereafter. Participants and their relatives will be provided with a comprehensive overview of the study protocol during the informed consent process. Individuals possess the right to decline participation without experiencing any adverse consequences regarding their treatment and standard of care.

The risk assessment generally encompasses the subsequent factors: 1. Surgical and Anesthetic Risks: Participants in this study will undergo posterior fossa tumor resection in the park bench position, which carries inherent surgical and anesthetic risks, including potential vascular injury, nerve injury, brain edema, respiratory complications, and hemodynamic instability. The procedures utilized in this research do not present additional risks beyond those typically associated with such surgeries. 2. Specific Risks Related to Research: The primary research intervention entails continuous hemodynamic monitoring through the use of central venous pressure (CVP) and pulse pressure variation (PPV). Complications associated with central venous and arterial catheters may arise during insertion or usage. These include pneumothorax, cardiac arrhythmias, arterial injury, infectious complications, and thrombotic complications. Preventing complications requires strict adherence to aseptic techniques during catheter insertion, appropriate site selection, utilization of ultrasound guidance to mitigate mechanical complications, and consistent monitoring of the catheter site.

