### Randomization and blinding

The schedule of enrolment, interventions, and assessments is shown in Fig 1. Patients will be randomly allocated to either CVP (group 1) or PPV (group 2)-guided fluid administration in a 1:1 ratio (Fig 2). Block randomization of block sizes 4, 6, and 8 was used to guarantee that the patient would be randomly and uniformly assigned to each group. A unique randomization code was generated from the website (sealedenvelope.com) by an independent research assistant [19]. The randomized code is sealed in an opaque envelope and will be opened when the patient arrives in the operating room.

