### Postoperative care

Post-surgery, all patients will be transferred to the neurosurgical ICU. The researchers will observe the patients for one week and will document data including the duration of intubation, the time point at which successful extubation, daily fluid balance, serum blood lactate, chest X-ray, and BUN/Cr values.

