#### Secondary outcomes.

Secondary outcomes are divided into intraoperative and postoperative data. Intraoperative data are (1) lowest systolic BP (mmHg), (2) blood loss during surgery (ml), (3) the requirement of vasopressors (no. and %), (4) urine output (ml), (5) serum lactate level (mg/dl), (6) brain relaxation score (percentage of a four-point scale), and (7) the incidence of extubation in the operating theater (no. and %). Postoperative data will be collected at the neurosurgical ICU, including (1) the length of time the patient is mechanical ventilation dependent (hours), (2) serum blood lactate, (3) chest X-ray, and BUN/Cr values and (4) The duration of the patient’s stay in the ICU (day).

Secondary outcomes are categorized as either confirmatory or exploratory to guide interpretation. Confirmatory secondary outcomes include serum lactate levels (intraoperative and postoperative), duration of ICU stay, and lowest systolic blood pressure. These outcomes will be analyzed with adjustments for multiple comparisons using Bonferroni correction. The remaining secondary outcomes, comprising less critical intraoperative variables such as brain relaxation score or urine output and postoperative variables such as chest X-ray abnormalities, are designated as exploratory. Exploratory outcomes will be reported descriptively and analyzed for hypothesis generation, without corrections for multiple comparisons.

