#### Primary outcome.

The primary outcome, the volume of intravenous fluid administered at multiple time points (t2 to t5), will be analyzed using a linear mixed-effects model (LMM) to account for repeated measures. Group (PPV vs. CVP), time (t2–t5), and interaction between group and time will be included as fixed effects, with a random intercept to account for within-patient correlation. Covariates will also be incorporated as fixed effects to adjust for potential baseline imbalances. For non-normal data, the generalized estimating equations (GEE) will be used.

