#### Secondary outcomes.

***Intraoperative data:*** Continuous variables (e.g., lowest systolic BP, blood loss, urine output) will be analyzed using an independent sample t-test or Mann-Whitney U test, as appropriate. Covariates will be adjusted using an analysis of covariance (ANCOVA). Categorical variables (e.g., vasopressor use, incidence of extubation) will be compared using the Chi-square test or Fisher’s exact test. For ordinal variables (e.g., brain relaxation score), a Mann-Whitney U test will be used.

***Postoperative data:*** For time-dependent outcomes (e.g., duration of mechanical ventilation, ICU length of stay), a Cox proportional hazards model will be used to estimate hazard ratios between groups (PPV vs. CVP), including baseline covariates to control for potential confounding. Kaplan-Meier survival analysis will be performed for graphical representation. Continuous variables (e.g., serum lactate levels, BUN/Cr values) will be compared using a t-test or Mann-Whitney U test, while categorical variables (e.g., chest X-ray abnormalities) will be compared using Chi-square or Fisher’s exact test. For repeated measures within the ICU (e.g., serum lactate levels over time), a linear mixed-effects model (LMM) will be applied.

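### The t-test or Mann-Whitney named for postoperative lactate, a confirmatory outcome, cannot use a pre-intervention value; this costs precision but causes no bias

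*Protocol article*

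**What the plan says.** Under Outcomes, Secondary outcomes, the article states: "Confirmatory secondary outcomes include serum lactate levels (intraoperative and postoperative), duration of ICU stay, and lowest systolic blood pressure". These outcomes carry a Bonferroni correction. Chest X-ray is exploratory, and BUN/Cr falls among the remaining, also exploratory, outcomes.

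On measurement, the Anesthesia protocol says: "Serum blood lactate levels will be evaluated hourly using arterial blood gas analysis throughout the surgical procedure". It also says: "Post-induction, a 20-G arterial catheter will be placed into the radial artery of the arm corresponding to the side of the lesion". The line is thus in place before the patient is positioned. The text does not give the time of the first sample relative to activation of the fluid protocol. Postoperative care lists "daily fluid balance, serum blood lactate, chest X-ray, and BUN/Cr values" among the items documented over one week. The full schedule is elsewhere: "The schedule of enrolment, interventions, and assessments is shown in Fig 1", and that figure is not in the text at hand.

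On analysis, the postoperative paragraph of Statistical analysis, Secondary outcomes, says: "Continuous variables (e.g., serum lactate levels, BUN/Cr values) will be compared using a t-test or Mann-Whitney U test". Chest X-ray abnormalities go to a chi-square or Fisher's exact test. The same paragraph applies a linear mixed-effects model (LMM) to repeated ICU values such as lactate. The ANCOVA sentence stands in the intraoperative paragraph. Adjustments and multiple comparisons adds a general provision for ANCOVA, Cox or LMM to deal with baseline imbalances, without listing covariates.

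**The concern.** Patients come to surgery with different lactate and creatinine values for reasons unrelated to the arm. The article itself mentions preoperative dehydration (Discussion) and steroids continued to the day of surgery (Preoperative preparation). A two-sample test on postoperative values leaves all of this variation in the error term. With about 25 patients per arm and a Bonferroni-reduced alpha, a confirmatory outcome has little precision to spare.

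The text also names two analyses for postoperative lactate, a simple test and an LMM, without saying which one is confirmatory. As described, neither includes a value from before the intervention.

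For the exploratory outcomes, the X-ray comparison has no stated rule that an abnormality must be new, so a finding already present before surgery could be counted.

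**Working it through.** **1. Can any analysis in the text use a pre-intervention lactate?**

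- t-test or Mann-Whitney on postoperative lactate and BUN/Cr: no. These tests take no covariate.
- LMM for repeated ICU lactate: it could, but the text describes it for ICU values and names no baseline term.
- ANCOVA: it could, but the sentence belongs to the intraoperative outcomes and names no covariate.
- General provision under Adjustments and multiple comparisons: it could, but it is framed as a response to imbalance and does not name lactate or creatinine.

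This comparison does not depend on Fig 1.

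**2. The plan's own sample size.** Sample size calculation gives 25 per group and 5% dropout: 25 / 0.95 = 26.3, rounded up to 27 per arm, or 54 in total. This agrees with the article. The 25 cannot be checked because no SD is given, and it concerns fluid volume. It is used here only as the number of patients available.

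**3. Detectable lactate difference.**

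Inputs:
- n = 25 per arm and 80% power, from Sample size calculation.
- Two-sided alpha = 0.05 / 4 = 0.0125. This is an assumption that counts intraoperative lactate, postoperative lactate, ICU stay and lowest systolic pressure as four tests.
- r, the correlation of baseline with outcome. No document gives it, so a range is assumed.

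Formula (normal approximation, in SD units): d = (z(1 − alpha/2) + z(0.80)) × √(2/n) × √(1 − r²).

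Without a baseline: (2.498 + 0.842) × √(2/25) = 3.340 × 0.2828 = 0.945 SD.

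| Assumed r | √(1 − r²) | d, 25 per arm | d, 27 per arm | Equivalent sample, 1/(1 − r²) |
|---|---|---|---|---|
| 0 (no baseline) | 1 | 0.945 | 0.909 | 1 |
| 0.3 | 0.954 | 0.901 | 0.867 | 1.10 |
| 0.5 | 0.866 | 0.818 | 0.787 | 1.33 |
| 0.7 | 0.714 | 0.675 | 0.649 | 1.96 |

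**4. Sensitivity to alpha.** If lactate counts once (0.05 / 3 = 0.0167), the figures at 25 per arm are 0.915 SD without a baseline and 0.873, 0.793 or 0.654 SD with one. At 0.05, the level relevant to exploratory BUN/Cr, they are 0.792 against 0.756, 0.686 or 0.566 SD. The proportional gain, √(1 − r²), depends on neither alpha nor n.

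**The case against.** The tempting stronger reading is that no lactate, BUN/Cr or chest X-ray is obtained before the intervention at all. The documents do not support it:

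- The schedule is in Fig 1, which cannot be seen.
- Hourly sampling from a line placed after induction is compatible with a first value before the fluid protocol is activated.
- The primary analysis covers t2 to t5, which implies an earlier time point.
- The preoperative section lists no blood test, yet the Fluid management protocol uses a preoperative hematocrit. That section is therefore not a full list of the work-up. Ethical considerations adds: "No additional blood work is required beyond the standard practice for patients undergoing SOC to remove tumors".

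A reader might also infer that a chance imbalance would invalidate the comparison. It would not. Under 1:1 randomization the comparison of post-treatment values has no systematic bias, and its standard error already allows for chance differences at baseline.

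It can further be said that the article plans LMM and ANCOVA adjustment, that covariate lists are commonly left to the analysis plan, and that the trial was not sized on lactate. This stands in part. The missing list is not the point. The point is that a test unable to take a covariate is named for a confirmatory outcome, and that the general provision does not commit to the pre-intervention value. The size of the gain does rest on an assumed correlation, and at 0.3 it is small.

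**Conclusion.** The point holds for the stated analysis. The text names an unadjusted test for postoperative lactate and BUN/Cr, and it designates no lactate sample before fluid-protocol activation as a baseline or covariate. Whether such a sample is scheduled remains open.

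The consequence is lost precision. With 25 per arm and alpha 0.0125, the unadjusted comparison detects 0.945 SD. A baseline with r from 0.3 to 0.7 would lower this to between 0.901 and 0.675 SD, a reduction of about 5% to 29%. These figures rest on the assumed correlations, the four-test Bonferroni count and a normal approximation.

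The main weight is on lactate. BUN/Cr and chest X-ray are exploratory. For the X-ray the issue is interpretation: whether an abnormality is new.

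**What to change.** - **Sample.** Confirm that the first arterial blood gas is drawn at arterial-line placement, before the group-specific fluid protocol is activated, and designate its lactate as the baseline. Time-stamp it: the allocation envelope is opened on arrival in the operating room, so the record must show that the sample precedes activation.
- **Lactate analysis.** Replace the t-test or Mann-Whitney with ANCOVA, or with an LMM for the repeated values. Include baseline lactate as a prespecified covariate whether or not imbalance is seen, and state which model is confirmatory. If lactate is skewed, a log scale can be used in place of the rank test. Use the same covariate for intraoperative lactate.
- **Exploratory outcomes.** Record routine preoperative BUN/Cr where available and use it as an ANCOVA covariate. Count a chest X-ray abnormality as an outcome only if it is new against any preoperative film.

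The cost is at most one time-stamped sample from a line already in place, plus a few case record form fields. Some patients will lack a preoperative BUN/Cr or film, so the plan should say how those missing baselines are handled.

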
### Fluid management protocol

CVP and PPV will be measured and recorded in both groups. Both parameters appear on the monitor screen throughout the operation. As a maintenance fluid, each patient will receive a weight-based formula of 0.9% normal saline solution and lactated Ringer solution [21]. Fluid management protocol will be activated, based on their assigned group (CVP or PPV), as shown in Fig 3. The treatment goal for the PPV group is a PPV value of less than 13%, whereas the treatment goal for the CVP group is a CVP value between 8–12 mmHg [22,23]. Before the implementation of the fluid management protocol, acute blood loss exceeding the permissible threshold and/ or hemoglobin < 9 gm/dl must be addressed and treated with pack red cell (PRC) transfusion [24]. The maximum allowable blood loss (MABL) is determined by considering gender, weight-based estimated blood volume, preoperative hematocrit, and the minimum acceptable hematocrit for the patient.

**Fig 3 pone.0324590.g003:**
[figure not shown]
Fluid management protocol.

### Postoperative care

Post-surgery, all patients will be transferred to the neurosurgical ICU. The researchers will observe the patients for one week and will document data including the duration of intubation, the time point at which successful extubation, daily fluid balance, serum blood lactate, chest X-ray, and BUN/Cr values.

### Outcomes

#### Primary outcome.

The primary outcome is the mean volume of intravenous fluids administered intraoperatively in the PPV group vs in the CVP group. The data will be represented in mean difference, 95% confidence interval, and p-value.

#### Secondary outcomes.

Secondary outcomes are divided into intraoperative and postoperative data. Intraoperative data are (1) lowest systolic BP (mmHg), (2) blood loss during surgery (ml), (3) the requirement of vasopressors (no. and %), (4) urine output (ml), (5) serum lactate level (mg/dl), (6) brain relaxation score (percentage of a four-point scale), and (7) the incidence of extubation in the operating theater (no. and %). Postoperative data will be collected at the neurosurgical ICU, including (1) the length of time the patient is mechanical ventilation dependent (hours), (2) serum blood lactate, (3) chest X-ray, and BUN/Cr values and (4) The duration of the patient’s stay in the ICU (day).

Secondary outcomes are categorized as either confirmatory or exploratory to guide interpretation. Confirmatory secondary outcomes include serum lactate levels (intraoperative and postoperative), duration of ICU stay, and lowest systolic blood pressure. These outcomes will be analyzed with adjustments for multiple comparisons using Bonferroni correction. The remaining secondary outcomes, comprising less critical intraoperative variables such as brain relaxation score or urine output and postoperative variables such as chest X-ray abnormalities, are designated as exploratory. Exploratory outcomes will be reported descriptively and analyzed for hypothesis generation, without corrections for multiple comparisons.

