### Sample size calculation

The primary outcome is the intraoperative fluid volume administered. The calculation of sample size utilized data from the research conducted by Janani Gopal et al [18]. The average fluid volume administration of patients in the CVP and PPV groups were 4,300 and 3,500 ml, respectively. In another study, the groups that used CVP guidance and those that used PPV guidance had a mean intraoperative fluid volume difference of 556 milliliters [25]. With the power of 80%, a 0.05 two-sided difference, the calculated sample size was 25 patients/group. Given a dropout rate of 5%, we will enroll 54 patients. The website clincalc.com is used to calculate the sample size. We anticipate a minimal drop-out and low loss to follow-up rate, as the study is conducted while the patient is under general anesthetic during surgery. Additionally, post-surgery, all patients will be admitted to the neurosurgical ICU, where we can gather data regarding the duration of their ICU stay.

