### Adjustments and multiple comparisons

To adjust for potential baseline covariate imbalances, specific analyses including ANCOVA, Cox proportional-hazards model, or LMM) will be used. To account for multiple comparisons across all secondary endpoints, a Bonferroni correction adjustment, will be applied.

A two-sided p-value of <0.05 will be considered statistically significant for the primary endpoint. The exploratory secondary analyses will report unadjusted p-values to guide future research. All statistical analyses will be performed using SPSS software by an expert statistician.

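### The confirmatory secondary outcomes are corrected by Bonferroni only among themselves, with no link to a primary tested at the full 0.05, and Holm's procedure would serve that set better

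*Protocol article*

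**What the plan says.** In the protocol article, the section on adjustments and multiple comparisons gives the rule for the primary: "A two-sided p-value of <0.05 will be considered statistically significant for the primary endpoint". The sample size section uses the same level: "With the power of 80%, a 0.05 two-sided difference, the calculated sample size was 25 patients/group". The primary therefore takes the whole 0.05.

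The secondary outcomes section divides the secondary outcomes into two classes, as a guide to interpretation. The first class is set out as follows: "Confirmatory secondary outcomes include serum lactate levels (intraoperative and postoperative), duration of ICU stay, and lowest systolic blood pressure". That is four outcomes, or three if lactate counts once. The correction follows: "These outcomes will be analyzed with adjustments for multiple comparisons using Bonferroni correction". The remaining outcomes are exploratory and uncorrected.

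The section on adjustments describes the family differently. It applies Bonferroni over every secondary endpoint, and then says that the exploratory analyses will report unadjusted p-values. Neither section gives the alpha for the secondary family or the Bonferroni divisor. Neither says whether the confirmatory secondary tests depend on the result for fluid volume.

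**The concern.** Calling a secondary outcome confirmatory tells the reader that an adjusted positive result may be taken as established. Under the stated rules that can happen whether or not fluid volume differs between the groups. The primary and the confirmatory secondaries are then two separate routes to a confirmatory claim, each with its own error allowance, and the two allowances add up.

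The practical risk is a trial with no difference in fluid volume but an adjusted positive result on ICU stay, lactate or blood pressure, reported as confirmed. Ordinary secondary outcomes would not raise the issue. It arises because these are singled out as confirmatory.

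There is also a simpler point of efficiency. Bonferroni is valid for the confirmatory set, but a method that is never less powerful gives the same protection.

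**Working it through.** **The plan's own figures.** The article states no error rate for the primary and confirmatory secondaries together, so there is none to reproduce. The sample size section shows only that the primary was given all of 0.05. Its dropout step is right: 25/0.95 = 26.3, rounded up to 27 per group, or 54 in all.

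**Inputs from the article.** Primary: two-sided 0.05. Confirmatory secondaries: m = 4, or m = 3 if lactate counts once. All secondary endpoints: 7 intraoperative plus 4 postoperative items = 11, or 12 if chest X-ray and BUN/Cr are split.

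**Assumptions.** The secondary family alpha is 0.05. Every null hypothesis is true. The correlation between test statistics is unknown and is varied.

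**Bonferroni within the confirmatory set, independent tests.** The rate is 1 − 0.95 × (1 − 0.05/m)^m.
- m = 4: 1 − 0.95 × (1 − 0.0125)^4 = 0.0966
- m = 3: 1 − 0.95 × (1 − 0.0167)^3 = 0.0967

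The upper bound under any correlation is 0.05 + m × 0.05/m = 0.10.

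**The same family with correlated tests.** Simulation of 1,000,000 null trials with equicorrelated normal test statistics:

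| Correlation | m = 4 | m = 3 |
|---|---|---|
| 0.3 | 9.2% | 9.2% |
| 0.5 | 8.3% | 8.5% |
| 0.7 | 7.1% | 7.3% |
| 0.8 | 6.3% | 6.6% |
| 0.9 | 5.5% | 5.7% |
| 1.0 | 5.0% | 5.0% |

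With m = 4 and correlation 0.5, about 8.3% − 5.0% = 3.3% of null trials would have a negative primary and a positive confirmatory secondary.

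**Bonferroni over every secondary endpoint, independent tests.** Only the four confirmatory outcomes can give a confirmatory claim.
- 11 endpoints: 1 − 0.95 × (1 − 0.05/11)^4 = 0.0672, bound 0.05 + 4 × 0.05/11 = 0.0682
- 12 endpoints: 1 − 0.95 × (1 − 0.05/12)^4 = 0.0657, bound 0.05 + 4 × 0.05/12 = 0.0667

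**With a gate on the primary.** If the primary null is true, any false claim requires a false positive primary, so the rate is at most 5%. If the primary effect is real, false claims come only from the secondary family, again at most 5%.

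**Holm against Bonferroni.** Holm compares the smallest p-value with 0.05/m, the next with 0.05/(m − 1), and so on, stopping at the first failure. Its first step is the Bonferroni test and its later thresholds are looser, so it rejects everything that Bonferroni rejects. As an illustration, take 27 per group, four outcomes that all have real effects, a normal approximation, and correlation 0 or 0.5. The effect sizes are assumed, because the article gives none for the secondary outcomes.
- Standardized effect 0.8: power per outcome 0.76 to 0.78 with Holm, 0.67 with Bonferroni
- Standardized effect 0.6: 0.45 to 0.46 with Holm, 0.38 with Bonferroni

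**The case against.** The strongest reply is that nothing stated here is invalid. Testing the primary at 0.05 and controlling error separately in a secondary family is a common and defensible choice. A hierarchy could also sit in an analysis plan that is not shown. This stands in part. The lack of a gate is not an error in itself, and whether to add one is a trade-off. It does not dispose of the point, because the article does not defer multiplicity. It sets out a scheme, attaches the word confirmatory to it, and keeps the primary outside the corrected family.

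A reader might infer that the trial promises 5% overall and delivers 8% to 10%. The documents do not support that, for four reasons.
- The only significance level given for testing is for the primary, whose own error rate is unaffected.
- The second 0.05 is inferred. On the broader family in the section on adjustments, the total is about 6.7%.
- The result depends on a correlation that the article does not give. It falls towards 5% as the correlation nears 1.
- The result needs a null primary. If the fluid difference that the design assumes is real, false confirmatory claims can come only from the secondaries, which Bonferroni holds to at most 5%.

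Nor does any section let a secondary outcome decide whether the trial has succeeded.

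It may also be said that preferring Holm is taste. Bonferroni is indeed valid. But Holm needs no further assumption and cannot reject less, so the preference has a reason.

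**Conclusion.** The point holds in a limited form. The confirmatory secondaries are corrected among themselves, the primary keeps the whole 0.05, and nothing connects the two. Under the global null, with an inferred secondary alpha of 0.05 and Bonferroni within the confirmatory set, the chance of at least one false primary or confirmatory claim lies between 5% and 10%: about 9.7% if independent and 8.3% to 8.5% at correlation 0.5. On the broader Bonferroni family it is about 6.7% if independent. This is an unstated property of the scheme and not a breach of a stated guarantee. Separately, the choice of Bonferroni gives up power in the confirmatory set for no gain in error control.

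**What to change.** **Method.** In both the secondary outcomes section and the section on adjustments, replace Bonferroni with Holm's step-down procedure at a stated two-sided family level, over the named confirmatory outcomes only. State whether lactate counts as one outcome or two. This also settles the two descriptions of the family. It costs nothing in error rate or power.

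Holm alone does not lower the joint rates above. Under the global null it makes a first rejection exactly when Bonferroni does.

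**Link to the primary, if joint 5% control is intended.** Add a sentence on these lines: the confirmatory secondary outcomes support confirmatory claims only if the primary is significant at two-sided 0.05; otherwise they are exploratory, reported with estimates, confidence intervals and unadjusted p-values. The cost is that no secondary can be called confirmatory after a failed primary, though it can still be reported. If joint control is not intended, say that error is controlled separately for the primary and for the confirmatory set.

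Either way, this is a few sentences to settle before unblinding, with no new patients or data.
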